### Sample Size Rationale

#### a) Clinical

Both LLINs and IRS alone reduce malaria morbidity by approximately 50% [5,6]. The combined impact of these two interventions is unknown. If the effects were simply additive a mean reduction of 75% could be anticipated for the combination, but the effects may be synergistic (e.g. by having a mass killing effect) or antagonistic (e.g. the repellency of DDT reducing *Anopheline *house entry and contact with LLINs). To cover these possibilities we expect that LLINs will reduce incidence by 50%, with LLINs and IRS combined reducing the residual incidence by 30-60% (i.e. 50% vs 65-80% fewer clinical cases of malaria). A study of 3-60 month old children during the end of the rainy season (Sept-Dec) in the URR in 2007 found a seasonal incidence of 0.79 (95% CI: 0.58-1.08) cases/child-years by PCD ([name] pers. comm.); ITN prevalence was 50%. We estimate conservatively that increasing LLIN provision to > 80% and inclusion of older children will reduce incidence rates by about 60-80%, so incidence rates of 0.30 (LLINs) to 0.15 cases/child-years (LLINs & IRS) have been included in the sample size estimations. The study will also record PCD over two high transmission seasons, not 1 as in the [name] study, further enhancing our ability to detect differences between study arms. Estimations for k, the corrected coefficient of variation to adjust for between cluster variation (based on within and between cluster variation) [27], from a cluster trial conducted in the Central River Region of The Gambia in 2006/7 ([name] personal communication) varied from 0.31-0.43 and has been used to explore sample sizes (Figure 2). Two of the 5 districts in URR have 70 villages suitable for the trial with over 100 children aged 6 months-14 years (predicted from the 2003 National Census) and could accommodate an average cluster size of 110 children (range 75-125). We plan to follow these children for 22 weeks covering the peak malaria incidence season each year, which, allowing for a 20% drop out rate over the 2 years, yields 74.4 child-years per cluster. The graphs below indicate a sample size of 5-39 clusters per arm (Figure 2). Since estimates for incidence and drop-out rate are conservative and the value of k may also be reduced by the stratified design, we will recruit 35 clusters in each arm of the trial.

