### Analytical plan

#### Outcome 1 - malaria morbidity

The primary endpoint is a comparison of the incidence of clinical episodes of malaria in children in the 2 intervention groups, measured by PCD. After a case of malaria is treated, time of observation will be censored for 3 weeks and further attacks of malaria during this period are not considered. History of travel away from the village for prolonged periods will be captured by monthly surveys and time at risk will be censored for such periods. In addition, malaria cases in children who resided outside their study village for more than half the elapsed study period at the time of illness will be censored. An initial unadjusted analysis will be based on comparisons of the incidence rates between the 2 groups. Incidence rates will be calculated for each cluster and the ratio of their un-weighted means will give an estimate of the intervention effects. Confidence intervals for the intervention effect will be obtained using the approximations given by Bennett [29] and tested using a bootstrapped [30] confidence interval. The incidence rates for each cluster will also be used to perform a hypothesis test based analysis between the 2 groups using a 2 sample unpaired t-test. It is likely that the rates will be highly skewed and if necessary the rates will be transformed. Using the incidence rates as a response, linear regression can be used to adjust for cluster level covariate effects. If the assumptions of normality and constant variance cannot be met, a non-parametric test (Mann-Whitney) will be used to compare the 2 groups. The cluster randomised trial will result in a multi-level model with individuals within village. Individual level covariates will be modelled using random effects Poisson regression which will be fitted using GLLAMM, a Stata program to fit generalized linear latent and mixed models GLLAMM [31], to allow for the clustering effect of village, compound and the effect of repeated episodes in the same child. Year will be included as a fixed effect which will allow any interaction with the intervention to be quantified. Other potential confounders such as house architecture, bednet use and recent antimalarial treatment will also be adjusted for in the analysis. Should the data, be zero-inflated or under/over dispersed modifications to the underlying distributional assumptions will be examined. The time to first infection will be examined using a survival analysis approach. Initial unadjusted analysis will use Kaplan Meier curves to compare the probability of subjects in the two arms becoming infected as the malaria season progresses. A Cox regression frailty model will be used to adjust for covariates, allowing for the clustering. The location of the infected subjects will be known to the household level and this information will be used to examine the spatial distribution of infection over time. Within the larger villages formal methods such as k-means fuzzy clustering [32] will be used to quantify clusters of infection.

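### Fuzzy k-means on case locations alone cannot separate clustered infection from housing layout; name a method that uses uninfected children and keep fuzzy k-means as description

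*Protocol article*

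**What the plan says.** The Analytical plan, Outcome 1 (malaria morbidity), ends with two sentences on space. The first gives the data: "The location of the infected subjects will be known to the household level and this information will be used to examine the spatial distribution". Change over the study period is included in that aim. The second gives the method: "Within the larger villages formal methods such as k-means fuzzy clustering [32] will be used to quantify clusters of infection".

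No other spatial method is named. The two sentences do not mention the locations of uninfected children, how the number of groups is chosen, or a comparison with what would be expected without clustering.

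The same section also plans a random-effects Poisson model, fitted "to allow for the clustering effect of village, compound and the effect of repeated episodes in the same child". That model uses the time at risk of all enrolled children.

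**The concern.** A cluster of infection means that infection is concentrated relative to where the children at risk live. Fuzzy k-means answers a different question: how best to divide a given set of points into a given number of groups. It has no null hypothesis and no population at risk.

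If it sees only cases, compact groups appear wherever compounds stand close together, even when every child has the same risk. Enrolment adds to this. Under Study area and participant eligibility, children are a random selection averaging 110 per cluster, so in a larger village case locations also reflect which households happen to hold enrolled children.

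What is at stake is what this one exploratory analysis can conclude. Groups of cases could be described as foci of infection when they only map the housing.

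**Working it through.** The article attaches no figure to this analysis, so there is none to reproduce. The check has three parts.

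**1. What the method can see.** Fuzzy k-means minimises the sum over cases *i* and groups *j* of u_ij^m × |x_i − v_j|², with the memberships u_ij of each case summing to 1. Its inputs are the points x_i, the number of groups and the fuzziness m. It returns the requested number of groups for any points. If r(s) is the risk at location s and n(s) the density of enrolled children, the density of cases is r(s) × n(s). Case locations inform only the product. Isolating r(s) needs n(s), hence the uninfected children. Choosing the number of groups by a validity index does not supply n(s), because such an index is computed from the same case points.

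**2. How many cases there would be.** Inputs from Sample Size Rationale, a) Clinical:
- Cluster size: "could accommodate an average cluster size of 110 children (range 75-125").
- Follow-up: 22 weeks per season for two seasons; "allowing for a 20% drop out rate over the 2 years, yields 74.4 child-years per cluster".
- Incidence: "incidence rates of 0.30 (LLINs) to 0.15 cases/child-years (LLINs & IRS) have been included in the sample size estimations".

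Child-years: 110 × (22/52) × 2 × 0.8 = 74.46, which agrees with the article's 74.4.

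Episodes per average cluster over both seasons: 74.4 × 0.15 = 11.2 and 74.4 × 0.30 = 22.3.

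At the top of the size range, 125 children: 125 × (22/52) × 2 × 0.8 = 84.6 child-years, giving 12.7 to 25.4 episodes. Restricting to larger villages therefore adds few points, because the number of enrolled children is capped.

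**3. Illustration.** Assumptions that are not in the article: 35 households in a 400 m square, placed either uniformly at random or in three clumps; 110 children assigned to households at random; 22 infected children, the upper figure above with each episode taken as a different child; and either equal risk or a sixfold risk weight within 80 m of one household. There were 150 villages per scenario. Fuzzy k-means used three groups and m = 2. It was summarised by the partition coefficient, the mean over cases of the sum of squared memberships, which runs from 1/3 (no structure) to 1 (crisp groups). The comparator was a permutation test on the mean distance between cases, redrawing 22 children from all 110, with 199 redraws, at the 5% level.

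| Housing | Infection | Partition coefficient, mean (5-95% range) | Permutation test rejects |
|---|---|---|---|
| Spread | random | 0.74 (0.66-0.80) | 5% |
| Spread | clustered | 0.76 (0.69-0.85) | 38% |
| Clumped | random | 0.85 (0.75-0.94) | 7% |
| Clumped | clustered | 0.82 (0.71-0.93) | 66% |

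Going from random to clustered infection moves the mean coefficient by 0.76 − 0.74 = +0.02 (spread) and 0.82 − 0.85 = −0.03 (clumped), with heavily overlapping ranges. Going from spread to clumped housing moves it by 0.85 − 0.74 = +0.11 (random infection) and 0.82 − 0.76 = +0.06 (clustered infection). The output tracks housing more than infection.

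The Monte Carlo standard error of a 5% rejection rate with 150 villages is √(0.05 × 0.95/150) = 0.018, so 5% and 7% both fit the nominal level.

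**The case against.** Most of the case on the other side limits the point rather than removing it.

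- *The method is an example.* The article says *such as*, so a scan statistic or a relabelling test is not excluded. This stands. Fuzzy k-means is nevertheless the only method offered as suitable, and it is the wrong kind of example for the purpose.
- *The aim may be descriptive.* To quantify clusters need not mean to test for them. A reader might infer that the plan uses fuzzy k-means to show whether infection is clustered, but the article does not say so. Even as description, however, groups of cases with no reference to the other children cannot be called clusters of infection.
- *Case-only input is inferred.* This stands. The article mentions only infected subjects' locations but does not define the algorithm's input. Details may lie in the cited reference or in a fuller plan, neither of which is shown.
- *Clustering is already modelled.* The compound random effect measures similarity within a compound using all children. It uses no coordinates, so it cannot show several neighbouring compounds forming a focus.
- *Nothing depends on it.* This stands. Spatial clustering appears in no objective, endpoint or sample size calculation.

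A reader might also infer that the two arms would be compared on their clusters, so that fewer cases under spraying would distort the comparison. The article plans no such comparison, and that harm should not be attributed to it.

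**Conclusion.** The point holds as a minor improvement. If fuzzy k-means is run on case locations alone, it will always produce groups, and by itself it cannot tell clustered infection from the layout of compounds with enrolled children. That the chosen number of groups is always returned is a property of the algorithm and needs no assumption. The sizes in the illustration rest on the assumed layout, the assumed risk pattern and 22 cases. With about 11, any method would have less power than the 38-66% shown.

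The documents do not support a stronger claim. They do not say that fuzzy k-means is the only method, that it serves as a test, or that results will be reported as proven foci. The primary and secondary endpoints, the randomised comparison and the sample size are unaffected.

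**What to change.** Reword the last sentence of Outcome 1. Name as the main method one that compares infected with uninfected enrolled children at their household locations under a null of no clustering. Suitable examples are a spatial or space-time scan statistic, or a Cuzick-Edwards or K-function difference test with random relabelling. Relabelling should respect compounds, because children in one compound share a location. Keep fuzzy k-means only to describe a pattern, and say so.

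The cost is a little more analysis and no change to endpoints or design. One thing needs confirming. Study children are enumerated, and their movements are assessed at monthly intervals through house visits, so their households should be identifiable, but the article does not state that locations are recorded for uninfected children. The downside is limited power at about 11-22 episodes per average cluster, and less for analyses by season or month. Some villages will show no detectable cluster, and that should be reported as such.

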
#### Outcome 2 - malaria transmission

Differences in malaria transmission experienced in the 2 groups will be made by comparing the mean number of mosquitoes caught indoors in houses between the intervention groups. Generalised estimating equations will be used to estimate differences in numbers of indoor-resting mosquitoes, adjusting for repeated measures within clusters and possible covariates.

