### Design

A cluster-randomized controlled study design will be used, as IRS is a community-level intervention and the village cluster as a suitable unit for randomization. All households in all the clusters will be offered LLIN at no cost to the recipients to enable all residents to benefit from this intervention. The clusters will then be randomized into two equal groups; all households in the villages in one group will be offered IRS and those in the other group will not. It is not possible to conduct the IRS in a blinded manner since a placebo would quickly be identified by the community as non-protective. To assess whether DDT IRS and LLINs combined provide better protection against clinical malaria in children than LLINs alone, 75- 125 children aged from 6 months to 13 years old will be sampled according to cluster size enrolled into a study cohort. These children will be followed during the malaria transmission season in 2010 and 2011. Clinical malaria will be recorded by study staff using PCD in close collaboration with government health workers both at the village and health facility levels. Parasites will be detected by a rapid diagnostic test (RDT, Paracheck Pf, Orchid Biomedical Systems, Goa, India) and treatment will follow government treatment guidelines.

The study cohort will be surveyed for malaria indices (parasite prevalence, anaemia and spleen rate) at the end of both transmission seasons to generate data for the secondary endpoints and also at baseline before the year 1 transmission season. Baseline data will be used to compare the 2 groups before the interventions and end of season survey data will be used to attempt to define a *Plasmodium falciparum *parasitaemia cut-off giving optimum sensitivity and specificity for malaria cases in this setting [14].

Exposure to malaria vector mosquitoes and parasites indoors will be assessed using CDC light traps and window traps every 4 weeks from June to December and every 8 weeks from January to May in at least 6 randomly selected households in 16 village clusters in each arm of the study. This will be followed by detection of *Anopheles gambiae *species, parity status and sporozoite infection. A schematic representation of the trial is shown in Figure 1.

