#### b) Entomological

Transmission parameters in the two arms of the study will be estimated from measurements made throughout the transmission season.

Primary: The mean number of female *An. gambiae *s.l./light trap/night inside sleeping rooms.

Secondary: The entomological inoculation rate (EIR) in each study group will be estimated as the mean number of sporozoite infective bites/child/season)

Tertiary: (i) The proportion of mosquitoes exiting houses (since DDT has repellent properties), (ii) the relative abundance of different members of the *An. gambiae *complex in light trap & exit traps collected in each arm of the trial, (iii) the relative abundance of *An. gambiae s.l. *collected outdoors (iv) the parity of *An. gambiae*, to measure mean population longevity.

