#### b) Entomological

Previous studies with experimental huts indicated that DDT IRS deterred 60-70% of mosquitoes from entering houses [28]. LLINs were not associated with a deterrent effect in Gambian houses [15]. Based on a study using light traps in an adjacent study area in 2005, we expect that the mean number of female *An. gambiae s.l. *per trap will be 4.8 (with a coefficient of variation, k = 0.44). In order to demonstrate a 60% reduction in hungry indoor mosquitoes (i.e. unfed *An. gambiae*) associated with DDT IRS, with 90% power and at the 5% level of significance, we would require 8 houses in each cluster and 12 clusters in each arm of the trial over 2 years [27]. Since the number of mosquitoes rise and fall during the rainy season we propose to sample from each house 6 times each year. To allow for loss to follow-up due to people moving house during the study period we propose to include at least 8 houses in each cluster and 15 clusters in each study arm for 2 years.

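### The primary entomological endpoint is analysed by GEE alone on 30-32 clusters; with the usual robust variance and normal reference, its nominal 5% test would run at about 7-8%

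*Protocol article*

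**What the plan says.** The primary entomological endpoint (Study endpoints, b) Entomological) is the mean number of female *An. gambiae* "s.l./light trap/night inside sleeping rooms".

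The Sample Size Rationale, b) Entomological, expects that the mean "per trap will be 4.8 (with a coefficient of variation, k = 0.44"). Its target is stated as "In order to demonstrate a 60% reduction in hungry indoor mosquitoes", and it concludes that, "with 90% power and at the 5% level of significance, we would require 8 houses in each cluster and 12 clusters in each arm". It then raises the plan to "at least 8 houses in each cluster and 15 clusters in each study arm for 2 years". On visits it says "we propose to sample from each house 6 times each year". The Design section instead has traps "in at least 6 randomly selected households in 16 village clusters in each arm of the study". The total is therefore 30 or 32 clusters.

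The only analysis named for this endpoint (Analytical plan, Outcome 2) is: "Generalised estimating equations will be used to estimate differences in numbers of indoor-resting mosquitoes, adjusting for repeated measures within clusters and possible covariates". No variance estimator, working correlation, reference distribution or covariate list is given.

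For the clinical primary endpoint (Outcome 1), the same plan calculates a rate for each cluster, applies a two-sample t-test to those rates, allows linear regression for cluster-level covariates and keeps a rank test in reserve. Mixed models come in addition. That endpoint has 35 clusters per arm, 70 in all.

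**The concern.** A GEE robust variance is estimated from the clusters, however many trap-nights lie inside them. With about 30 clusters it is too small on average, and comparing the Wald statistic with a normal distribution ignores the uncertainty in that variance. Both faults push the same way, and each cluster-level parameter in the model adds to them.

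The plan thus gives the method most sensitive to few clusters to the outcome with fewer than half as many clusters, without the cluster-summary test that it gives to the other primary outcome. At stake is the claim that spraying reduces indoor vector density when the true effect is nil or small: the interval for the density ratio would be somewhat too narrow, and significance would be declared more often than the 5% used in the sizing.

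**Working it through.** **Inputs from the article.** Control mean m0 = 4.8; 60% reduction, so m1 = 0.4 × 4.8 = 1.92; k = 0.44; 5% level (two-sided assumed, as the article does not say); 90% power; 8 houses; 6 visits in each of 2 years, so 12 visits; 15 clusters per arm with 8 houses, or 16 with 6.

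**1. The plan's own figure.** The cluster-trial formula for means is

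c = 1 + (z₀.₉₇₅ + z₀.₉₀)² × [(s0² + s1²)/n + k²(m0² + m1²)] / (m0 − m1)².

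- (1.96 + 1.282)² = 10.51
- m0² + m1² = 23.04 + 3.69 = 26.73
- k² × 26.73 = 0.1936 × 26.73 = 5.17
- (m0 − m1)² = 2.88² = 8.29

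The within-cluster SD is not given, so 12 per arm cannot be derived from the stated inputs alone. Poisson variation with n = 8 gives 1 + 10.51 × (0.84 + 5.17)/8.29 = 8.6, so 9. A within-cluster SD equal to the mean gives 1 + 10.51 × (3.34 + 5.17)/8.29 = 11.8, so 12. The plan's 12 is consistent with a within-cluster CV of about 0.90-1.02. The sizing is not in dispute; what matters here is its 5% level.

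**2. Closed form, no covariates.** With n clusters per arm, the uncorrected robust variance is (n − 1)/n times the unbiased one. A normal-reference test therefore rejects when |t| on 2n − 2 df exceeds 1.96 × √((n − 1)/n).

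| Clusters per arm | Threshold applied | Correct t value | False-positive rate | Interval width, used/correct |
|---|---|---|---|---|
| 15 | 1.96 × √(14/15) = 1.894 | 2.048 (28 df) | 6.9% | 0.92 |
| 16 | 1.96 × √(15/16) = 1.898 | 2.042 (30 df) | 6.7% | 0.93 |

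Scaling the variance by N/(N − 1), N being all clusters, leaves 6.3-6.4%.

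**3. Simulation under no effect.** Log-link GEE with the village cluster as the independent unit and gamma between-cluster variation with CV 0.44. The within-cluster variation is assumed, because the article does not give it: negative binomial catches with dispersion 1.2 in one set (4,000 runs per setting), a between-house CV of 1 in the other (10,000 runs, or 6,000 for house-level covariates). Ranges cover both sets and both layouts unless noted.

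| Model | Robust variance, normal reference | Kauermann-Carroll, t | Mancl-DeRouen, t |
|---|---|---|---|
| No covariates | 7.0-7.9% | 5.0-5.9% | 4.2-5.2% |
| 4 cluster-level df | 9.5-10.7% | 5.3-6.2% | 3.3-3.6% |
| 7 cluster-level df | 11.9-13.6% | 5.1-6.2% | 2.3-2.8% |

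Linear regression of log cluster means gave 4.7-5.3% across these models (first set only). With 0, 2 and 4 house-level covariates, the uncorrected test at 15 per arm gave 8.3%, 7.4% and 8.1%. The simulation error there is about √(0.08 × 0.92/6000) = 0.35 points, so there is no trend.

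The 4 df correspond to the stratifiers in the Randomisation section: health centre presence (1) and four areas (3).

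**4. Power for the planned effect.** |ln 0.4| = 0.916. From between-cluster variation alone, the standard error at 15 per arm is √(2 × 0.1936/15) = 0.161, so the effect is 5.7 standard errors. Adding a between-house CV of 1 over 8 houses gives √(2 × (0.1936 + 0.125)/15) = 0.206, or 4.4 standard errors. Simulated power (negative binomial set, 4 cluster-level df) was at least 99.9% under every method.

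**The case against.** The strongest reply is that the article does not describe an uncorrected test. It names GEE and stops there. Variance estimator, degrees of freedom and small-sample correction are details that a condensed article commonly leaves to the analysis plan, which is not shown, and GEE for repeated trap counts is not wrong in itself. This stands in part: the absence of a correction cannot be held against the text, and every inflated figure above is conditional on the default being used.

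A reader might go further and infer that the trial's actual false-positive rate is 7%, rising to 9-13% once covariates are added. The documents do not support that. The upper range needs several cluster-level covariates (12-14% needs all seven stratum dummies), and the Outcome 2 section commits to none. The covariates listed as examples under Secondary endpoints, such as house design and net use, are at individual or house level, where no added inflation was seen. Nor does any section say that the stratifiers enter this model.

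It is also fair that the excess is modest and that a true 60% reduction would be detected by any of these methods.

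What the reply does not remove is the choice itself. The article gives test-level detail for the clinical outcomes, including a cluster-level test for the one with 70 clusters, and names only GEE for the one with 30-32. GEE as ordinarily run misses the stated 5% level at that number.

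**Conclusion.** The point holds as a conditional one. If the standard robust variance and normal reference are used, the nominal 5% test of the primary entomological endpoint has a false-positive rate of about 7-8%, and its interval is about 7-8% too narrow on the log scale. Adjusting for the four stratifier degrees of freedom would raise the rate to about 10%. This is not a demonstrated error in the level of the test that will be run.

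The closed form assumes a two-sided test and roughly normal cluster-level residuals. The simulated figures rest on k = 0.44 and the assumed within-cluster variation; raising k to 0.6 left the unadjusted rate at 7.7%. The disagreement between 15 clusters of 8 houses and 16 clusters of 6 does not alter the conclusion. The consequence is confined to a nil or small true effect and does not touch the clinical primary endpoint.

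**What to change.** In the Outcome 2 section, state one of the following as the test of the primary entomological endpoint.

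- **Cluster-level analysis.** A t-test, or a linear regression, of log cluster mean catch on arm, with the stratification factors included if the analysis is adjusted. This matches the approach in Outcome 1 and held 4.7-5.3% in simulation. It estimates a ratio of geometric means of the cluster means, which should be said. A rule for a cluster with no catch should be given, though about 1.92 × 72 = 138 mosquitoes are expected per sprayed cluster even with 6 houses and 12 visits.
- **Corrected GEE.** Keep the GEE with the village cluster as the independent unit, a small-sample corrected robust variance (Kauermann-Carroll, for example) and a t reference on the number of clusters minus the number of cluster-level parameters. Kauermann-Carroll gave about 5-6%. Mancl-DeRouen is also acceptable but becomes conservative as cluster-level covariates are added.

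Under either option, name the cluster-level covariates in advance and keep them few. The change is wording only, with no extra traps or data. The interval becomes slightly wider, and power for the planned 60% reduction stays above 99% under the assumptions shown.
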